#### Statistical analysis of MRI data

In each group, longitudinal hierarchical linear models will be used to assess changes over time of WM tract DTI measures and average Z-scores of RS functional connectivity (FC), accounting for the repeated measurement design. Statistical analyses of VBM, TBM, MRI active and RS FC maps derived from ICA will be performed using the SPM12 software (whole brain analysis, *p* < 0.05, family-wise error [FWE], corrected for multiple comparisons).

Voxelwise differences of MD, RD, AD and FA values between groups at baseline, and their within-group changes at follow up will be tested using a permutation method (“Randomize” program within FSL) and two-sample and paired t tests, as appropriate (*p* < 0.05 FWE).

Linear regression analysis (using SPM12) will be used to assess the correlations between fMRI activations, RS FC maps and clinical and neuropsychological data.

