## Abstract

**Background:**

Cognitive dysfunction affects up to 70% of people with progressive MS (PMS). It can exert a deleterious effect on activities of daily living, employment and relationships. Preliminary evidence suggests that performance can improve with cognitive rehabilitation (CR) and aerobic exercise (EX), but existing data are predominantly from people with relapsing-remitting MS without cognitive impairment. There is therefore a need to investigate whether this is also the case in people with progressive forms of the disease who have objectively identified cognitive impairment. It is hypothesized that CR and EX are effective treatments for people with PMS who have cognitive impairment, in particular processing speed (PS) deficits, and that a combination of these two treatments is more effective than each individual treatment given alone. We further hypothesize that improvements in PS will be associated with modifications of functional and/or structural plasticity within specific brain networks/regions involved in PS measured with advanced MRI techniques.

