### Aim, design and setting of the study

The study has the following primary aims:
To assess whether CR and exercise (EX) in combination have beneficial synergistic effects in the treatment of impaired processing speed in people with PMS.To determine whether CR and EX are individually effective treatments for impaired processing speed in people with PMS.

Secondary aims:
To assess the everyday life impact of cognitive and/or physical changes after the different rehabilitation interventions.To assess brain functional and structural substrates of cognitive changes after the different rehabilitation interventions.

This study is a multicenter, multi-arm, randomized, double-blinded, sham-controlled trial that includes follow up periods of 12- and 24 weeks (+/− 2 weeks) post randomization. As depicted in Fig. 1, after the baseline assessment each participant will be randomized to one of four arms with different combinations of CR and EX and their respective shams (−S). That is: CR + EX; EX + CR-S; EX-S + CR; EX-S + CR-S.

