#### Brain MRI protocol

Brain MRI scans will be obtained using 3.0 Tesla scanners. Budgetary constraints dictate that the MRI is obtained in one third of the sample (i.e. 120 subjects divided equally (*n* = 30) between the four treatment arms). The following sequences will be collected at baseline, termination of the interventions and after 24 weeks of follow up, following a standardized protocol of acquisition and careful guidelines for patients repositioning: axial T2 weighted Turbo Spin Echo (TSE); axial FLAIR; high resolution 3D sagittal T1-weighted sequence; axial DT sequence (55 contiguous, 2.5 mm thick, slices, #DW direction = 64) and T2*-weighted single-shot echo-planar imaging (EPI) during and active cognitive fMRI task and at rest.

For active fMRI, the Go/No-go task will be administered using a block-design, as previously described [66]. Reaction times, omission errors (no response although required), commission errors (false response without adequate cue), and the proportion of correct responses will be recorded using a response-box. Before imaging, participants will be familiarized with the paradigm. The fMRI Go/no-Go paradigm has been used both in cross-sectional [67] and longitudinal [68] studies of people with MS. Notably, a longitudinal (median follow up 20 months) neuropsychological and fMRI evaluation detected significant correlations between worsening of SDMT performances and modification of activation during the Go/no-Go task in several supra- and infratentorial brain regions [68]. Most importantly, the Go/no-Go task has already been validated for multicentric acquisition [66]. During resting state (RS) fMRI, subjects will be instructed to remain motionless, to close their eyes and not to think about anything in particular. Movements will be minimized using foam padding and ear blocks.

The total duration of MRI acquisition (structural plus functional MRI) will be approximately 50 min.

MRI analysis: MRI data acquired for the study will be analyzed centrally at one Neuroimaging Research Unit (Hospital San Raffaele, Milan, Italy).

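### For the diffusion and resting-state connectivity measures, change is tested within each arm, and no between-arm contrast of change is named

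*Protocol article*

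**What the plan says.** All references are to the protocol article.

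- **Aim.** Under Aim, design and setting of the study, one secondary aim reads: "To assess brain functional and structural substrates of cognitive changes after the different rehabilitation interventions". The Abstract (Background) adds the hypothesis that "improvements in PS will be associated with modifications of functional and/or structural plasticity within specific brain networks/regions" involved in processing speed. The Abstract (Methods) lists MRI among the secondary outcome measures.
- **Data.** Under Brain MRI protocol, "MRI is obtained in one third of the sample (i.e. 120 subjects divided equally" with 30 per arm. On timing: "The following sequences will be collected at baseline, termination of the interventions and after 24 weeks of follow up".
- **Tract and connectivity summaries.** Under Statistical analysis of MRI data: "In each group, longitudinal hierarchical linear models will be used to assess changes over time of WM tract DTI measures". Average RS FC Z-scores are covered by the same sentence.
- **Voxelwise diffusion maps.** The same section plans to test "Voxelwise differences of MD, RD, AD and FA values between groups at baseline, and their within-group changes at follow up", using permutation and "two-sample and paired t tests, as appropriate".
- **Grey matter.** Brain MRI protocol assigns voxel-based morphometry (VBM) to between-arm differences at baseline, and tensor-based morphometry (TBM) to regional change over time, without saying which groups are contrasted.
- **Other maps.** For VBM, TBM, active fMRI and the ICA-derived RS FC maps, the statistics section gives the software and the family-wise error (FWE) control but no contrast. The thalamic seed analysis refers to changes in the study groups without saying between or within.
- **General rule.** The last paragraph of Statistical analyses says that secondary outcomes are handled like the primary one, by ANOVA and ANCOVA.

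**The concern.** The question in the aim is comparative: what happens in the brain after different interventions. For the tract DTI measures, the RS FC Z-scores and the voxelwise diffusion maps, the analysis described for change is not comparative. Each arm is set against its own baseline. For the voxelwise maps, the between-arm test is placed at the one time point where randomisation already makes the null hypothesis true.

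A within-arm change combines any intervention effect with everything else that moves between scans: elapsed time, scanner drift and the course of a progressive disease. The double-sham arm shares all of these and is there to subtract them. The article uses that logic elsewhere. Its Power analysis relies on learning effects cancelling when mean changes are compared across arms, and its Discussion explains that the exercise sham was chosen to limit its own influence on brain function.

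At stake is a report that tract integrity or connectivity changed in, say, the combined arm and not in sham, read as an effect of the combination although no test of that difference was made.

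**Working it through.** **Inputs**

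- Arms: 4, with 120/4 = 30 per arm, and 120/360 = one third of the trial (Brain MRI protocol).
- Significance level: 5%, two-sided (Statistical analyses).
- Within-arm power p and standardised change d for an MRI measure: not in the article, so assumed and shown over a range.

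**The plan's own figure.** The article gives no power figure for MRI. Its SDMT figure reproduces: noncentrality = 90 x [(4-2)² + 0 + 0 + (0-2)²] / 8² = 90 x 8/64 = 11.25 on 3 and 356 df, which gives power 0.80885 as in Table 6. It does not bear on the MRI analyses.

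**Step 1: where each comparison is placed**

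- Tract DTI measures and RS FC Z-scores: change within each arm; no between-arm contrast named.
- Voxelwise MD, RD, AD and FA: between arms at baseline; within arms at follow-up.
- VBM: between arms at baseline.
- TBM, active fMRI, ICA maps, thalamic RS FC: contrast not stated.

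**Step 2: how often separate tests disagree when the arms do not differ.** Assume one summary measure, independent arms, the same true change in all four and an uncorrected 5% test in each.

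P(some arms significant, others not) = 1 - p⁴ - (1-p)⁴

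- No change, p = 0.05: 1 - 0.000006 - 0.814506 = 0.185
- p = 0.50: 1 - 0.0625 - 0.0625 = 0.875
- p = 0.80: 1 - 0.4096 - 0.0016 = 0.589

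The most misleading pattern is sham not significant with at least one active arm significant. Its probability is (1-p) x [1 - (1-p)³].

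- p = 0.05: 0.95 x 0.142625 = 0.135
- p = 0.50: 0.50 x 0.875 = 0.438
- p = 0.80: 0.20 x 0.992 = 0.198

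**Step 3: the same by size of the shared change** (paired t-test, n = 30, noncentral t)

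- d = 0.2: p = 0.185, disagreement 0.558
- d = 0.37: p = 0.50, disagreement 0.875
- d = 0.5: p = 0.754, disagreement 0.673
- d = 0.8: p = 0.988, disagreement 0.045

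The risk is highest for moderate shared change and disappears once every arm is almost certain to be significant.

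**Step 4: comparator.** In 20,000 simulated trials at each of d = 0, 0.2, 0.37 and 0.5, separate tests disagreed in 18.4%, 56.0%, 87.5% and 67.3%. One ANOVA of change across the four arms rejected in 4.7% to 5.2%. That 5% belongs to a single omnibus test. Three uncorrected factorial tests (CR, EX, CR x EX), if independent, would give 1 - 0.95³ = 14%.

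**Step 5: what between-arm tests can detect** (80% power, two-sided 5%)

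- Two single arms, 30 v 30: 0.74 SD of change.
- Factorial main effect, 60 v 60: 0.52 SD (0.516 before rounding).
- CR x EX as a difference of differences: its standard error is √(4/30) = 0.365 SD, against √(2/60) = 0.183 SD for a main effect. It therefore needs about 2 x 0.516 = 1.03 SD.

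**The case against.** The strongest reply is that a between-arm route already exists. The Abstract lists MRI as a secondary outcome, and Statistical analyses sends secondary outcomes to ANOVA and ANCOVA, as for the primary outcome. This stands in part: the document is unclear rather than uniformly silent. However, the MRI section is separate and sets its own models, and nothing says whether it replaces the general rule or adds to it.

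Second, part of the MRI objective is association: whether gains in processing speed go with brain change. The MRI section plans regressions of fMRI activation and RS FC on clinical and neuropsychological data, which address that hypothesis. This stands, and those regressions should stay. They do not test whether the arms change differently.

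Third, the analysis plan, which is not shown, may supply the contrast. That would excuse an omission. Here the article states within-arm testing as its choice.

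Fourth, the percentages describe a reader's mistake, and nowhere does the article say that disagreement between arms will be read as a difference. This is fair. The figures show how easily the mistake would arise and are not an error rate of a declared test. Voxelwise FWE control would alter them, but separate within-arm maps would still not test arm differences.

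A reader might go further and infer that the whole sub-study compares arms only at baseline and cannot attribute any brain change to an intervention. The article does not support that. For TBM, active fMRI, ICA maps and thalamic connectivity no contrast is given, and a condensed article may leave that to the full plan. Randomisation and the double-sham arm do allow attribution once a between-arm contrast of change is specified. Practice on the Go/No-go task is no argument here either, since it concerns active fMRI, for which no within-arm test is stated.

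**Conclusion.** The point holds for three sets of measures: tract DTI, average RS FC Z-scores and the voxelwise diffusion maps. For these, the stated tests of change do not use the sham control and do not answer the comparative part of the secondary aim. The fault lies in the stated analysis, not in the design or the data collected.

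The 18.5% figure needs only four independent 5% tests and no true change. The 87.5% and 59% figures also rest on assumed within-arm powers of 50% and 80%, which the article does not give. The baseline comparisons add little but do not bias the estimates of change. The primary SDMT result is untouched. The wording should be corrected before the MRI data are analysed.

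**What to change.** For these three sets of measures:

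1. Fit one longitudinal model per summary measure over all MRI participants, with CR, EX, CR x EX, their interactions with time, and site/scanner. Adjust for the baseline value in one of two ways, not both. If the baseline scan is the first repeated response, inference rests on the arm-by-time terms. If it is a covariate, inference rests on the arm contrasts at the follow-up scans.
2. Test the overall arm difference in change first, then the factorial contrasts with multiplicity control across the three.
3. For voxelwise diffusion data, run the permutation tests on change maps between arms, FWE-corrected.
4. Label within-arm results and baseline between-arm comparisons, including the VBM one, as descriptive.
5. Keep the planned regressions for the association hypothesis.
6. State that the ANOVA/ANCOVA rule for secondary outcomes applies to MRI.

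The cost is wording; scans and software stay the same. The price is power. With 30 per arm, between-arm contrasts will be significant less often than within-arm tests might suggest. The factorial main effects are the most efficient contrasts, and the CR x EX interaction will be estimated imprecisely. The report should say so and give confidence intervals.

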## Discussion

The present study will be the first combined CR and exercise trial to date in persons with PMS with the potential to change clinical practice; this trial further is the largest combined CR and exercise study in any MS phenotype. As the study is a large international multicenter study, efforts have been made to ensure trial feasibility. Moreover, the collaborating sites have access to patient populations that should allow sufficient recruitment. Efforts have been made to ensure optimal standardization and subsequently best possible data quality. Such efforts relate to 1) comprehensive and detailed assessment and intervention manuals as well as a combination of face-to-face and distance training on how to deliver these, 2) weekly quality control and feedback of the delivered interventions, 3) hotlines in case of questions relating to delivery of the interventions and 4) weekly telephone conferences allowing the widely dispersed centers close communication.

There are well described challenges related to the development of appropriate sham interventions when it comes to exercise trials [84, 85]. Adding to this challenge is the fact that the underlying mechanisms mediating potential exercise induced effects on brain function are poorly understood [86]. A sham-concept that does not significantly improve cardio-respiratory function but still involves attentional and social contact components was therefore chosen as a counterweight to the aerobic exercise intervention [13]. Choosing the appropriate sham treatment is important as it limits the potential of this intervention to alter brain function that is known to accompany aerobic exercise.

The imaging component to our study broadens the scope of our inquiry. MRI techniques are currently being applied to investigate mechanisms related to structural and functional brain plasticity in healthy individuals following training and in neurologically impaired individuals following spontaneous recovery and after rehabilitation interventions. Several authors have used fMRI during active tasks or at rest to evaluate the effects of motor [87, 88] and cognitive [18, 36, 89–92] rehabilitation in MS patients. All of these studies have demonstrated that a modulation of function in brain regions have a crucial role in the trained function which occurs in MS after rehabilitation and is associated with clinical improvement. Whether such changes are possible in people with PMS, is not yet known. Our study therefore has the potential to address the dearth of data in this population and shed light on the degree to which neural plasticity is retained in the context of a progressive disease course.

The impact of cognitive dysfunction in the lives of people with MS is considerable. It is associated with difficulties finding and sustaining employment, maintaining intimate relationships and friendships, pursuing leisure activities and managing basic activities of daily living [93]. Given that we have chosen a primary outcome measure, namely the SDMT, in which a 10% (or 4-point) change over time is known to be clinically significant, should our interventions achieve this threshold, they will acquire the imprimatur of an elusive ecological validity. Moreover, the multinational composition of the research teams all pursuing a shared methodology has the potential to demonstrate that the chosen interventions can transcend language, cultural and indeed institutional barriers that make it difficult to extrapolate results from only a single centre.

The study is expected to conclude by the end of 2022. With a robust sample size that ensures adequate statistical power, the findings, if positive, have the potential to guide clinically meaningful interventions for people with PMS who struggle with all the functional limitations associated with slowed processing speed.

## Data Availability

At completion of the study, only the data coordinating center at Washington University will have access to the final dataset. At conclusion of the study, results will be communicated through individual MS societies from each participating country.

## Abbreviations

ACSM: American College of Sports Medicine
AD: Axial Diffusivity
AHA: American Heart Association
ANART: Adult National Reading Test
ANCOVA: Analysis of Covariance
ANOVA: Analysis of Variance
BDN-II: Beck Depression Inventory – II
BICAMS: Brief International Cognitive Assessment for MS
BVMT-R: Brief Visuospatial Memory Test-Revised
CMI: Cognitive-Motor Interference
CNS: Central Nervous System
CPET: Cardiopulmonary Exercise Test
CR: Cognitive Rehabilitation
CSF: Cerebrospinal Fluid
CVLT: California Verbal Learning Test
CT: Continuous Training
DCT: Dual Task Cost
EDSS: Expanded Disability Status Scale
EPI: Echo-planar Imaging
EQ -5D-5L: European Quality of Life – 5 Dimensions
EX: Exercise
FA: Fractional Anisotropy
FAMS: Functional Assessment of Multiple Sclerosis
fMRI: Functional Magnetic Resonance Imaging
GLTEQ: Godin Leisure-Time Exercise Questionnaire
GM: Grey Matter
GMV: Grey Matter Volume
HADS: Hospital Anxiety and Depression Scale
HIIT: High Intensity Interval Training
HR: Heart Rate
ICA: Independent Component Analysis
IET: Incremental Exercise Test
IQ: Intelligence Quotient
LSD: Lysergic Acid Diethylamide
MD: Mean Diffusivity
MFIS: Modified Fatigue Impact Scale
MNI: Montreal National Institute
MRI: Magnetic Resonance Imaging
MS: Multiple Sclerosis
MSIS-29V2: Multiple Sclerosis Impact Scale – 29 Items Version 2
MSWS-12: Multiple Sclerosis Walking Scale 12 Items
NART: National Adult Reading Test
NBV: Normalized Brain Volume
PCP: Phencyclidine
PDQ-20: Perceived Deficits Questionnaire 20 Items
PI: Principal Investigator
PMS: Progressive Multiple Sclerosis
PPMS: Primary Progressive Multiple Sclerosis
PRO: Patient Reported Outcomes
PS: Processing Speed
QALY: Quality Adjusted Life Year
RD: Radial Diffusivity
RPE: Rate of Perceived Exertion
RRMS: Relapsing Remitting Multiple Sclerosis
RS: Resting State
RSFC: Resting State Functional Connectivity
-S: Sham
SD: Standard Deviation
SDMT: Symbol Digit Modalities Test
SPMS: Secondary Progressive Multiple Sclerosis
TBM: Tensor-based Morphometry
TBSS: Tract-based Spatial Statistics
TSE: Turbo Spin Echo
VBM: Voxel-based Morphometry
W: Watt
WM: White Matter
WMV: White Matter Volume
WR: Work Rate
WTAR: Wechsler Test of Adult Reading
6-MWT: Six Minute Walk Test
